**Methods:**

A total of 60 healthy volunteers in the age group of 20 to 40 years who fulfill the selection criteria will be recruited for this randomized controlled trial at the National Ayurveda Institute for Panchakarma, Cheruthuruthy, Kerala, India, and randomized in a 1:1 ratio to either the intervention group (n=30; group 1, receiving *nasya karma* with *anu taila*, an oil-based formulation manufactured using a paste and decoction of herbal medicines with oils as the base material, for a period of 14 days) or the control group (n=30; group 2, not receiving any intervention). The participants will undergo task-based and resting fMRI on day 1 (twice on day 1 before administration and 15 minutes after *nasya karma* for participants in group 1) and day 14 to map the neurophysiological response to *nasya karma* of the brain. A comprehensive neuroimaging protocol using structural magnetic resonance imaging and fMRI will be used in the study. The effect of *nasya karma* on sleep, psychological well-being, cognition, and quality of life will be assessed on the 1st and 30th days in both groups.

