*Panchakarma* encompasses a comprehensive set of Ayurvedic detoxification procedures, including *vamana* (emesis), *virechana* (purgation), *nasya* (nasal administration of herbal oils or powders), *basti* or *vasti* (herbal enema), and *raktamokshana* (bloodletting) [6]. *Panchakarma* is a mainstay of Ayurveda clinical practice where the physician can choose any of the 5 sets of therapeutic modalities to bring about a homeostatic equilibrium in the body tailored to each individual depending on the intended purpose of use (promotive, preventive, therapeutic, or rehabilitative), body constitution, *dosha* (the body humors or functional principles that govern physiological and psychological processes), health or disease status, age, and fitness to undergo the *panchakarma* procedure.

*Anu taila* [7] is an oil-based formulation manufactured using a paste and decoction of herbal medicines with oils as the base material. The ingredients are combined in specific proportions as highlighted in classic Ayurvedic texts and subjected to a unique heating process to meet certain pharmaceutical parameters, ensuring the retention of both water-soluble and lipid-soluble principles at optimal levels. *Anu taila* can be likened to liposomes, where nanoparticles comprise lipid bilayer membranes surrounding an aqueous interior. The higher viscosity of this formulation increases contact time between the drug and the nasal mucosa, thereby enhancing permeation, and the viscosity may influence mucociliary clearance, potentially reducing it and, thus, prolonging the formulation’s retention time in the nasal cavity, which can lead to increased drug absorption [8,9].

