### Interventions

The participants in the intervention group will be administered *nasya karma* (nasal instillation) with *anu taila* at a dose of 3 mL per nostril for 7 days (on every alternate day for 14 days) as indicated in the Ayurveda treatises for healthy individuals. Before *nasya*, local oleation and sudation of the head region will be conducted for approximately 10 minutes. Following the *nasya karma* procedure, participants will inhale medicated smoke and rinse their mouths with lukewarm water. The control group, consisting also of healthy individuals, will not undergo any interventions to facilitate assessment of the specific effects attributed to *nasya karma* in the intervention group when compared to baseline measures in healthy individuals.

*Nasya karma* will be administered by the investigator at the hospital’s *panchakarma* unit except on assessment days, when it will be conducted at AIMS. Each participant will be closely monitored for 30 minutes following the procedure to observe any immediate effects or reactions. Vital signs such as heart rate, blood pressure, and respiratory rate will be monitored and recorded before and after every session. Participants reporting any adverse symptoms experienced after each session will be recorded through a standardized format designed to capture a wide range of potential side effects, including nasal irritation, headache, dizziness, nausea, or any other discomfort. Any serious adverse event will be reported immediately to the institutional ethics committee, and a causality assessment will also be conducted. Appropriate care will be provided for all adverse events requiring medical intervention, and they will be followed up on until resolution or stabilization.

If a participant experiences significant adverse effects, such as severe nasal irritation, fever, sinusitis, or any other serious discomfort that impacts their well-being, the intervention will be immediately halted, and the participant will be withdrawn. Discontinuation will also occur in cases of noncompliance with the treatment regimen, if the participant wishes to withdraw for any reason, or if the participant meets any of the exclusion criteria during the study. As the trial involves healthy volunteers, administration of concomitant medication is prohibited during the trial period of 30 days.

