### Primary Outcome Measure

The primary outcome measure for this study is the BOLD signal detected via fMRI in specific brain regions that are associated with motor, sensory, memory, and cognitive circuits elicited during both the rest and task phases. A 3-Tesla MRI scanner will be used to assess the brain’s response to different stimuli at multiple time points: before the *nasya karma* procedure, immediately before the *nasya karma* procedure, immediately after (within 15 min) the *nasya karma* procedure, and on the 14th day of the *nasya karma* therapy.

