### Detailed Methodology of the Primary Outcome Measure

#### Overview

The primary outcome measure encompasses 2 key components. The first is the assessment of the immediate neurophysiological response elicited by *nasya karma* during both the resting and task phases using MRI. The second component is the evaluation of the neurophysiological response elicited by *nasya karma* after 14 days (following 7 days of nasya) during both the resting and task phases using MRI. Functional neuroimages will be collected using a 3-Tesla scanner (Discovery MR750w; GE HealthCare). Resting state fMRI data will include 3D T1-weighted structural imaging with a fast-spin echo sequence and BOLD imaging with a spin echo, gradient echo, and echo-planar imaging sequence for 40 minutes, covering the entire brain. The parameters for 3D-T1 imaging will include a slice thickness of 1 mm; a repetition time and echo time of 8.5 milliseconds and 3.2 milliseconds, respectively; a field of view of 256 × 256 × 142 mm^3^; a flip angle of 12°; a matrix of 256 × 256; an in-plane resolution of 1 × 1 × 1 mm^3^; and 142 layers. The parameters for BOLD imaging will include a slice thickness of 3.2 mm; a repetition time and echo time of 3000 milliseconds and 30 milliseconds, respectively; a flip angle of 80°; a matrix of 64 × 64; a field of view of 256 × 256 × 142 mm^3^; 35 layers; and 150 time points.

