##### fMRI Data Analysis

The fMRI data will undergo preprocessing using either the Data Processing and Analysis for Brain Imaging or CONN toolboxes, which will encompass essential steps such as slice timing correction, realignment for motion correction, regression to remove confounding effects, normalization to a standard template, smoothing to enhance signal-to-noise ratio, detrending to remove low-frequency drifts, and filtering to focus on relevant frequency bands, aligning with established practices in the field. After data preprocessing, amplitude of low-frequency fluctuation, functional connectivity, and large-scale functional brain network analysis will be conducted to investigate the difference in neurophysiological responses between the groups. The results will be interpreted in the context of the experimental paradigm to elucidate neural correlates of the studied phenomena, providing insights into the effects of *nasya karma* on brain function. Voxels exhibiting expected time-course correlations (30-second periods) will receive high activation scores, whereas those showing no correlation or deactivation will receive lower or negative scores, respectively. MRI data analysis will use general linear models via statistical parametric mapping (SPM). fMRI data will be processed using MATLAB 2023 (MathWorks Inc).

Resting phase MRI data will be analyzed using software tools such as SPM, the CONN toolbox, and the Functional Magnetic Resonance Imaging of the Brain Software Library (Analysis Group), whereas task phase fMRI will specifically use SPM. Given the focus on group data in this study, complex patterns of brain activation will be interpreted collectively rather than individually. For voxel-based analysis, a significance threshold of *P*<.01 at the voxel level and *P*<.05 corrected for false discovery rate (FDR) at the cluster level will be applied. Connectome-based analysis will use a threshold of *P*<.05 corrected for FDR. Additionally, Pearson correlation analysis will be performed to explore potential associations between clinical outcomes and fMRI findings, examining changes in brain activity following different interventions.

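### The immediate pre-post EPI comparison exists only in the nasya group, and none of the named processing steps would show whether residual oil or mucosal change in the nose altered the signal near the skull base

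*Protocol article*

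**What the plan says.** **Instillation.** Under Interventions, the active group receives anu taila "at a dose of 3 mL per nostril for 7 days", on alternate days. Inhaled medicated smoke and a mouth rinse follow each session.

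**Retention.** The Background states "The higher viscosity of this formulation increases contact time between the drug and the nasal mucosa". It adds, in hedged terms, that viscosity may slow mucociliary clearance and so lengthen "retention time in the nasal cavity, which can lead to increased drug absorption".

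**Timing.** The Abstract puts the day-1 scans of group 1 as "twice on day 1 before administration and 15 minutes after" nasya. Primary Outcome Measure places the second scan no more than 15 minutes after the procedure. Resting Phase fMRI says it follows once the whole procedure is finished, and Preparatory Phase gives the procedure about 30 to 45 minutes.

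**Acquisition.** The Overview of the primary outcome methodology specifies a 3 T scanner and echo-planar BOLD with "a repetition time and echo time of 3000 milliseconds and 30 milliseconds, respectively", on a 64 × 64 matrix over 256 mm.

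**Comparator.** In Table 1 the control group is scanned once on day 1 and once on day 14. Controls receive no instillation.

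**Processing and reading.** The fMRI Data Analysis section names "essential steps such as slice timing correction, realignment for motion correction, regression to remove confounding effects, normalization to a standard template", then smoothing, detrending and filtering. It plans amplitude of low-frequency fluctuation (ALFF), connectivity and network analyses, and interprets the results as neural correlates.

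**The concern.** Echo-planar images are displaced and lose signal where air meets tissue, and the nasal cavity lies just below orbitofrontal and olfactory cortex. If oil takes the place of some air, or the mucosa swells, the local static field differs between the two day-1 scans. Signal in ventral frontal voxels can then move, fade or return without any change in neural activity, and ALFF and connectivity computed there can change with it.

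Two features of the design make this matter. The immediate contrast is pre-post within one arm, so there is no control rescan from which to subtract such a change. And the effect would tend to act in a similar way across treated participants, so cluster-level familywise error or false discovery rate thresholds, which control chance findings, give no protection.

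At stake is the reading of one region in one of the two primary components. The Background argues for direct delivery along olfactory and trigeminal pathways, so an artefact just above the nose could pass for confirmation.

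**Working it through.** The article gives no figure on this point, so there is nothing of its own to reproduce. The check asks only whether the effect could matter at the stated imaging settings.

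**From the article**
- Instilled volume: 3 mL × 2 nostrils = 6 mL, the ceiling for what can remain.
- In-plane voxel: 256 mm / 64 = 4 mm.
- Field strength: 3 T.

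**Assumed, not in the article**
- Proton frequency at 3 T of 127.7 MHz.
- Susceptibility difference between air and oil of 9.4 ppm.
- Retained oil modelled as one sphere of volume V and radius a.
- A point at distance r from its centre, directly above it along the main field.
- EPI readout of 20, 32 or 45 ms (32 ms is 64 lines at 0.5 ms).
- No re-shimming.

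**Formulas**
- Field shift (Hz) = (9.4/3) × 2 × 127.7 × (a/r)³ ≈ 800 × (a/r)³, with a³ = 3V/(4π).
- Displacement (mm) = field shift × readout time (s) × 4 mm.

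Example, V = 1 mL and r = 2 cm: a³ = 0.239 cm³, (a/r)³ = 0.239/8 = 0.0298, shift = 23.9 Hz. At 32 ms the displacement is 23.9 × 0.032 × 4 = 3.1 mm.

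| Retained | Distance | Shift (Hz) | Displacement at 20 / 32 / 45 ms (mm) |
|---|---|---|---|
| 0.3 mL | 2 cm | 7.2 | 0.6 / 0.9 / 1.3 |
| 0.3 mL | 4 cm | 0.9 | 0.1 / 0.1 / 0.2 |
| 1 mL | 2 cm | 23.9 | 1.9 / 3.1 / 4.3 |
| 1 mL | 3 cm | 7.1 | 0.6 / 0.9 / 1.3 |
| 1 mL | 4 cm | 3.0 | 0.2 / 0.4 / 0.5 |
| 3 mL | 2 cm | 71.6 | 5.7 / 9.2 / 12.9 |
| 3 mL | 4 cm | 9.0 | 0.7 / 1.2 / 1.6 |
| 6 mL | 4 cm | 17.9 | 1.4 / 2.3 / 3.2 |

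**Volume needed for a shift of one voxel.** The field must reach 1/readout, which is 50, 31.25 or 22.2 Hz. At 2 cm, dividing by 23.9 Hz per mL gives 2.1, 1.3 or 0.9 mL. At 3 cm, dividing by 7.1 Hz per mL gives 7.0, 4.4 or 3.1 mL; the first exceeds the 6 mL instilled. At 4 cm even the full 6 mL stays below one voxel. To the side of the sphere the field is half as large, so the required volume doubles.

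Signal loss was not computed; it depends on slice orientation and shim, which are not stated.

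**What the named steps do.** Slice timing concerns acquisition order. Realignment corrects rigid head motion. Detrending and filtering act within a run. Smoothing spreads a local change. Normalization may absorb part of a smooth displacement, but it neither reports one nor restores lost signal. Confound regression is not described further; as usually applied it works on the time course within a run and leaves a difference in static field between scans untouched.

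**The case against.** The strongest reply is that nothing quoted is wrong. The processing list is introduced as examples, the article condenses a fuller protocol, and field maps, shimming or dropout checks may stand in documents not shown. A reader might infer that the trial has no distortion correction; the article does not support that. This part of the reply stands.

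A reader might also infer that scanning starts within 15 minutes of the oil entering the nose. It does not say so: the 15 minutes run from the end of the procedure, and the interval from instillation to scan is not stated. Nor does the Background say that oil fills the airspace. Its remark on clearance is hedged, concerns contact with the mucosa, and gives no residual volume.

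The calculation leans towards a large effect. Oil from two nostrils is merged into one sphere, and re-shimming is ignored although participants return to the MRI room for the second scan. The same formula gives 143 Hz, or about 18 mm, for 6 mL at 2 cm with a 32 ms readout. That requires that no oil has drained or been swallowed, and it should not be read as an estimate.

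Finally, the exposure is narrow. The article names motor, sensory, memory and cognitive circuits and does not name orbitofrontal cortex. Static distortion partly cancels within a task run. Table 1 places nasya on days 1 to 13, so the day-14 scan is less exposed.

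These objections limit the size and reach of the point but do not remove it. Mapping is planned across the whole brain, the immediate comparison has no control counterpart, and the steps that are named would not show the change. A correction step elsewhere would reduce displacement but would not restore lost signal, so a before-after check would still be useful.

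**Conclusion.** The concern holds as an unaddressed, intervention-specific risk of unknown size. The documents establish the instillation, the argument for prolonged contact, the 3 T echo-planar sequence and the uncontrolled day-1 pair. They do not establish how much oil remains, or that any result will be an artefact.

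Under the stated assumptions and before re-shimming, the displacement is negligible for small residues or at 4 cm with 1 mL or less. It approaches or exceeds one 4 mm voxel only if about 1 mL or more remains within about 2 cm, with the exact volume depending on the readout time. The results mainly at risk are resting-state amplitude and connectivity in ventral frontal areas at the immediate time point. Within-run task contrasts are less affected, although signal loss can still change their sensitivity between scans. Confidence in the magnitude is low; that the named steps would not show such a change does not depend on it.

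**What to change.** Prespecify a check to be run before the immediate-response contrast:

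- In the nasya group, compare normalized mean EPI images from the two day-1 scans in ventral frontal and skull-base regions, for signal level and for geometric alignment to the participant's T1 image.
- Set the threshold for a relevant change in advance from the control group's day 1 to day 14 variation, which is the only between-session variation without oil in this design. It spans a longer interval than the day-1 pair, and the report should say so.
- Report immediate effects in voxels beyond the threshold as not interpretable as neural.

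Do not use temporal signal-to-noise ratio as the masking criterion. Its denominator is the temporal standard deviation, which includes the low-frequency fluctuation that ALFF measures. Masking on it would select on an outcome and could delete genuine effects anywhere in the brain.

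If the full imaging protocol already contains a field map or distortion correction, name it in the analysis section; the check is still worth keeping because correction does not recover lost signal.

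The cost is a small analysis step on images the plan already collects, with no change to treatment or scanning. The downside is that some ventral frontal voxels may drop out of the immediate result.

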##### Multiple-Comparison Correction

For voxel-wise analyses, statistical inference will be performed with the following corrections. At the voxel level, uncorrected *P*<.001 will be used as an initial threshold. At the cluster level, familywise error (FWE) correction (*P*<.05) will be applied to control for multiple comparisons across the brain. In parallel, FDR correction will be applied where appropriate to control the expected proportion of false positives. For independent component analysis–based network analyses, dual regression outputs will be thresholded using FWE correction (*P*<.05). This combination ensures robust control of type I error.

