##### Power Analysis

A priori power analysis was conducted using G*Power (version 3.1) and the fMRIPower toolbox. On the basis of pilot data and prior studies of similar paradigms, an expected effect size of Cohen *d*=0.6 (moderate) was used. For a voxel-level threshold of *P*<.001, uncorrected and cluster-level FWE of *P*<.05, and a sample size of 30 per group, the analysis achieves >80% power to detect activation differences in relevant cortical regions. This power analysis informed our sample size and statistical thresholds.

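### Two incompatible significance rules are stated for the same voxelwise maps of the primary outcome, and the claim of robust type I error control goes beyond what either rule delivers

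*Protocol article*

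**What the plan says.** All the statements are in the Statistical Analysis part of the protocol article.

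- **fMRI Data Analysis:** "For voxel-based analysis, a significance threshold of *P*<.01 at the voxel level and *P*<.05 corrected for false discovery rate (FDR) at the cluster level". The same paragraph gives connectome-based analysis its own FDR threshold of P<.05.
- **Multiple-Comparison Correction**, for voxel-wise analyses: "At the voxel level, uncorrected *P*<.001 will be used as an initial threshold". For clusters, the section goes on to say that "familywise error (FWE) correction (*P*<.05) will be applied to control for multiple comparisons across the brain". A further sentence then reads: "In parallel, FDR correction will be applied where appropriate to control the expected proportion of false positives". Dual regression outputs from the independent component analysis are thresholded by FWE at P<.05. The section ends: "This combination ensures robust control of type I error".
- **Power Analysis** uses only the second rule: "For a voxel-level threshold of *P*<.001, uncorrected and cluster-level FWE of *P*<.05, and a sample size of 30 per group". It adds that the power analysis informed the statistical thresholds.
- **Correlation of Clinical Outcomes and fMRI Data** applies Benjamini-Hochberg at q<0.05 across the correlations. This is the only correction across separate tests that the article states.

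The primary outcome is the BOLD signal in several circuits at rest and on task (Primary Outcome Measure). It has two components, immediate and after 14 days (Detailed Methodology of the Primary Outcome Measure, Overview).

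**The concern.** The two rules are unconditional and cover the same analyses. Nothing assigns one to rest and the other to task, or makes one a sensitivity analysis. Because they govern the primary outcome, they decide which clusters are reported as positive. With two rules and an open-ended third option, an analyst who has seen the maps could follow the plan and still choose the rule that gives a finding.

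The closing sentence on type I error adds a second problem. A reader of the results would take it as covering the primary outcome as a whole, whereas the stated correction covers one brain map at a time.

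**Working it through.** **1. The two rules side by side**

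| | fMRI Data Analysis | Multiple-Comparison Correction |
|---|---|---|
| Scope | voxel-based analysis | voxel-wise analyses |
| Voxel level | P<.01 | P<.001, uncorrected |
| Cluster level | FDR, P<.05 | FWE, P<.05 |
| Extra clause | none | FDR in parallel, condition not stated |
| Used for the power statement | no | yes |

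**2. Size of the threshold gap.** The ratio is .01/.001 = 10. For a two-sample contrast with 30 per group (df = 30 + 30 − 2 = 58, complete data, no covariates), the one-sided critical t is 2.39 at .01 and 3.24 at .001.

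The cluster-level rates also differ. FWE limits the chance of any false cluster in the map. FDR limits the expected share of false clusters among those declared, and it does not limit the chance of any false cluster once some effects are real. A broad, weak cluster can pass the first rule and fail the second, so the two rules can give different lists of findings from the same data.

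**3. What the FWE correction covers.** It is defined across the brain, hence within a map. The article lists five task paradigms (visual, auditory, right motor, left motor, memory) and three resting metric families (amplitude of low-frequency fluctuation, functional connectivity, network analysis). It also has two time components. Assumed counts from these:

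- one metric at two time components: k = 2
- 5 + 3 analyses at one time component: k = 8
- 8 × 2: k = 16

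With each map held at .05 and independence assumed, the chance of at least one false-positive map is 1 − 0.95^k:

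| k | Independent maps | Lower bound (fully dependent) | Upper bound (.05 × k) |
|---|---|---|---|
| 2 | 9.8% | 5% | 10% |
| 8 | 33.7% | 5% | 40% |
| 16 | 56.0% | 5% | 80% |

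Under a complete null, a valid FDR procedure at .05 also gives a 5% chance of any false positive. The illustration therefore does not depend on every analysis using FWE.

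**4. The plan's own power figure.** The article states more than 80% power, and "an expected effect size of Cohen *d*=0.6 (moderate) was used". A single two-sample t test with d = 0.6 and 30 per group has power 14.2% at two-sided .001 and 19.5% at one-sided .001, so this proxy does not reproduce the stated figure. It is not cluster-level power, which needs smoothness and spatial extent that the article does not give. That is a separate question. The power statement is used here only to show which rule the design was built on.

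**The case against.** The strongest reply is that the document already points to a rule. The section devoted to multiple comparisons and the power section agree on P<.001 with cluster FWE, so only one sentence is out of line. That stands, and it makes the repair easy. It does not remove the conflict, because the outlying sentence says that its rule will be applied, and the parallel-FDR clause sits inside the section that is meant to settle the matter.

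A second reply is that the trial is exploratory by title and by its sample size rationale. Such a study need not correct across maps or name one primary map, and a condensed article may leave such detail to a fuller document. That also stands. The lack of correction across maps is not the finding here. What remains is a positive claim of robust control that the stated procedure does not support beyond a single map.

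Three stronger readings are tempting, and the documents do not support them:

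- **That the trial's familywise error is 56%.** This rests on an assumed 16 independent maps. Maps from the same participants are correlated. The immediate component has no concurrent control scan, so its contrasts are within-group and not equivalent to those at day 14. The figure would also be the same after the threshold conflict was resolved.
- **That the looser voxel threshold lets through ten times as many false findings.** The tenfold ratio applies to voxels before cluster correction. Both rules then correct at .05 at the cluster level.
- **That a single primary map must be named.** The primary outcome deliberately spans rest, task and two time components. Reducing it to one contrast would change the design.

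**Conclusion.** The contradiction is established from the text alone. Two voxelwise decision rules, with a tenfold difference in cluster-forming threshold and a different cluster-level error rate, apply to the same primary-outcome analyses, and nothing says which one decides. The undefined parallel-FDR clause widens the choice. This should be settled before any map is analysed.

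The claim of robust type I error control is also unsupported as worded. Control is within a map, and the only correction across separate tests is for the clinical-imaging correlations. The 9.8%, 33.7% and 56% figures show the direction and possible scale under assumed counts and independence. They are not estimates of this trial's error rate. The exploratory purpose lowers the need for control across maps, but it excuses neither the conflict nor the claim.

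**What to change.** 1. In fMRI Data Analysis, delete the voxel P<.01 with cluster-FDR rule. Use voxel P<.001 with cluster-level FWE P<.05 for every voxelwise map, as Multiple-Comparison Correction and Power Analysis already do. Adopting this rule does not endorse the stated power.
2. In Multiple-Comparison Correction, delete the parallel-FDR sentence for voxelwise maps. Keep FDR for the connectome analysis and for the correlations.
3. Replace the robust-control sentence with wording such as: error is controlled within each map and not across tasks, resting metrics and time points; results across maps are exploratory.

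**Cost:** these are text edits, with no change to data collection. The downside is that fewer clusters may pass the stricter rule. Naming one primary contrast is optional. It would give a single confirmatory test, but it is a design choice that alters the primary outcome, and it should be decided as such and not made as an edit.
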